### Wave design and randomisation

As winter was the crucial period for the study, and recruitment is often slow at the start of the process the study was deliberately designed to recruit over two years in ‘waves’. Participants were recruited from three communities from 2009 to early 2011. Those recruited (i.e. consent and baseline data received) by June (early winter in the southern hemisphere) 2010 were assigned to Wave 1, those recruited later were assigned to Wave 2. Each wave was randomised into early and late intervention groups – the early group receiving the intervention the first winter in which the wave was enrolled in the study, and the late group the following winter. Thus *Wave 1- Early* participants received the fuel subsidy during 2010; *Wave 1- Late* and *Wave 2- Early* participants received the subsidy during 2011; *Wave 2- Late* participants received the subsidy during the winter of 2012. The randomisation was carried out by a statistician external to the study team.

The configuration of an autumn baseline with a spring follow-up was chosen in recognition of the significant illness of the sickest participants; with a full winter baseline there could have been more of a bias towards only the least unwell people completing the study. We allowed for a greater drop-out rate than we usually experience due to the illness among the study population.

As the intervention was carried out at a dwelling level, in order to avoid clustering, we selected only one primary participant per household, the person best able to complete the study questionnaire. The baseline interviews were carried out before randomisation so that knowledge of their group allocation could not affect the participants’ measures. In order to utilise the voucher for additional heating, the participants were then informed of their group allocation. Although the interviewers also knew the participant’s group allocation, they were trained to avoid mentioning group allocation status during interactions with the participants to minimise any recall bias. The analyses will be carried out with the researchers blinded to the meaning of the intervention group code. We also included several indicators designed to measure each participant’s propensity to report positive change and will control for the placebo effect by conducting sensitivity analyses using these propensity to positivity scores.

The flow of participants through the study is summarised in Figure 1, and the wave design portrayed in Figure 2.

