### Setting

The study was set up in three predominantly low-income urban areas. This study was carried out in partnership with local organisations with an interest in health and housing [44]. These organisations included a Māori health provider, a District Health Board, and Primary Health Organisations. Two communities were in the lower North Island (Whanganui and Wellington) and one in the South Island (Christchurch). Contracts were negotiated with these providers, who then worked closely with the research team, employing local field workers, nurses or community nurses, trained to conduct spirometry and administer the questionnaires.

One of the community organisations, Tu Kotahi, a Māori Asthma and Respiratory provider operating under the umbrella of Kokiri Marae, a large urban-based *marae* (communal meeting place), has participated in our two previous community housing trials. Our partnership is seen as resulting in many positive outcomes for both parties. For the Tu Kotahi Māori community it has brought insulated homes, improved heating, minimising the effects of allergens and increased information about healthy housing; for the University researchers it has provided access to the considerable knowledge of the community, as well as capacity building for both individual researchers and research groups.

Tu Kotahi’s involvement in housing research projects has highlighted the effects of poor housing on the health of their *whānau* (extended family community). In 2007, Tu Kotahi established a Māori COPD support programme and an important aspect has been the focus on healthy housing. Being research partners in this study has enabled Tu Kotahi to work more closely with *whānau* in their homes to assess their health status prior to, during and following the winter period, which has brought benefits beyond the study participation.

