“The opportunity to follow up utilising our own community health worker has been crucial to maintaining the majority of *whānau* on the study. We have experienced a transient population during the study and this has often meant that we have only been able to locate *whānau* with information provided by the community health worker’s networks. Often, we discover that [members of the] *whānau* have been hospitalised or they have had to travel home for *tangihanga* (funerals). We also discovered how socially isolated a number of *whānau* are, this sometimes involved numerous visits before the door was opened for the community health worker to complete the study questionnaire and tests. We were also saddened at the number of *whānau* who passed away during the study; many of the *whānau* who participated experienced other co-morbidities that impacted on their respiratory conditions.”

The South Island provider, Community and Public Health, is the public health unit for the region of Canterbury. Staff also had a well-established working relationship with the researchers. Since 2001, these staff also carried out their own local health promotion strategies connected to housing improvement. Working with the researchers was therefore considered a mutually worthwhile undertaking in terms of developing opportunities for public health action.

In September 2010 the first of a continuing series of earthquakes and aftershocks occurred in Christchurch and the surrounding area [67]. With considerable fortitude the Christchurch team did not let the earthquake, aftershocks or widespread liquefaction disrupt the spring visits by the field workers. In February 2011 a major earthquake caused a massive collapse of buildings and 185 lives were lost [68].

Workplaces in the CBD were severely damaged and the area was closed to the public. The city’s infrastructure was in chaos as hundreds of organisations and businesses had no premises to work from, including the staff of Community and Public Health. This had an impact on the WHEZ study in a number of ways and the community researchers set about trying to overcome the subsequent problems.

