### Data analysis

Generalised linear models will be fitted to the data. Covariates potentially included in the model will be study arm, current medication, age, sex, region, baseline severity, smoking status and immunisation status (influenza and pneumococcal). The appropriateness of a Poisson or negative binomial model of exacerbations will be confirmed by examining the residuals of the observed data fitted to the postulated models against an envelope of residuals from a set of simulated trials. If the observed residuals fall inside the simulated envelope then the model is considered to fit adequately. A non-parametric test – rank analysis of covariance – will be used to confirm differences between the groups.

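### Allocation was randomised within wave, but neither wave nor winter is among the listed model covariates: a small loss of precision, not a bias

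*Protocol article*

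**What the plan says.** Under Wave design and randomisation, the protocol article defines the waves by recruitment date: "Those recruited (i.e. consent and baseline data received) by June (early winter in the southern hemisphere) 2010 were assigned to Wave 1", and later recruits formed Wave 2. It then states "Each wave was randomised into early and late intervention groups". Early participants were subsidised in their wave's first winter and late participants in the next. Wave 1's first winter was therefore 2010 and Wave 2's was 2011. Of the Wave 2 late group the article says "participants received the subsidy during the winter of 2012". No other stratification factor is stated.

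Under Data analysis, the article gives one covariate list: "Covariates potentially included in the model will be study arm, current medication, age, sex, region, baseline severity, smoking status and immunisation status". It contains no wave, year or winter, and no term that lets a region's rate change over time.

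Under Setting, the article describes the sites: "Two communities were in the lower North Island (Whanganui and Wellington) and one in the South Island (Christchurch". It also reports: "In September 2010 the first of a continuing series of earthquakes and aftershocks occurred in Christchurch and the surrounding area". A major earthquake followed in February 2011 and large aftershocks in June 2011. Homes and heating were damaged, some participants relocated, and the rule on moving house was relaxed for Christchurch only. The article does not say how the analysis will treat this.

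**The concern.** An analysis should normally condition on the factor within which allocation was randomised. Wave is that factor here, and in a first-winter comparison it is also the calendar year. Winters may differ in weather, circulating infection and electricity price, all of which could move exacerbation rates. If wave is left out, that variation goes into the residual, the model's standard error no longer matches the randomisation, and an uneven early share between waves passes into the estimate.

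The earthquakes raise a related point. Region is listed, but a region main effect is a single constant. Christchurch before September 2010 and Christchurch afterwards would share one coefficient, although housing and heating there changed in between.

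At stake are some precision, slightly conservative inference, and protection against chance imbalance. The trial enrolled 522 against a target of 550, so modest precision is worth keeping.

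**Working it through.** **Inputs.** From the article (Sample size, Abstract): exacerbation rate 1.13 per year, rate ratio 0.75, negative binomial k = 0.46, 239 per arm, 522 enrolled. The text gives neither wave sizes nor the allocation ratio, so equal waves and the wave and earthquake effects below are assumptions. The plan has no figure of its own on this point to reproduce.

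**1. Which winter holds whom**

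| Winter | Wave 1 | Wave 2 | Relative to September 2010 |
|---|---|---|---|
| 2010 | first winter, Early subsidised | not yet started | before |
| 2011 | second winter, Late subsidised | first winter, Early subsidised | after |
| 2012 | – | second winter, Late subsidised | after |

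In a first-winter analysis, wave and calendar year coincide, and Christchurch-by-wave is the same as Christchurch-after-September-2010. With second winters included, neither identity holds: winter 2011 contains both waves, and Wave 1 Christchurch participants fall on both sides of the first earthquake.

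**2. Balanced allocation.** 600 trials were simulated per scenario: 478 participants (2 × 239), two equal waves, 1:1 within wave, three equally likely regions, and one yearly count each with variance m + 0.46m². Negative binomial models were fitted. Cells show the mean model standard error of the log rate ratio, then the percentage of trials rejecting at two-sided 5%.

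| True rate ratio; wave effect; extra Christchurch–Wave 2 factor | arm + region | + wave | + wave × region |
|---|---|---|---|
| 0.75; 1.0; 1.0 | 0.1119; 71.3 | 0.1118; 71.5 | 0.1118; 72.5 |
| 0.75; 1.25; 1.5 | 0.1067; 78.0 | 0.1052; 78.2 | 0.1049; 79.2 |
| 0.75; 1.5; 2.0 | 0.1059; 76.8 | 0.1011; 79.8 | 0.1001; 81.0 |
| 1.00; 1.5; 2.0 | 0.1018; 3.8 | 0.0969; 5.2 | 0.0958; 5.7 |

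- Where the true ratio is 0.75, the estimated ratio is 0.752 to 0.755 in every model, so there is no bias.
- In the third row, adding wave lowers the standard error by 1 − 0.1011/0.1059 = 4.5%, and adding wave × region by 1 − 0.1001/0.1059 = 5.5%. In the second row the figures are 1.4% and 1.7%. In the first row there is essentially no change.
- In the null row without wave, the mean standard error of 0.1018 exceeds the observed spread of the estimates, 0.0983, by 3.6%. With wave the two are 0.0969 and 0.0979. Rejection of 3.8% against 5% is suggestive only (Monte Carlo error √(0.05 × 0.95/600) = 0.9 points), but it has the direction expected when a stratum is ignored.
- Power of 71–73% with no wave effect is below the plan's 80%. That is a separate question and does not affect the comparison between models.

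**3. Unequal early share.** Take equal waves, no treatment effect, early share s in Wave 1 and 1 − s in Wave 2, and wave rate ratio w. The crude rate ratio is [s + (1 − s)w] / [(1 − s) + sw]. For s = 0.55 and w = 1.5 it is (55 + 67.5)/(45 + 82.5) = 122.5/127.5 = 0.961.

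| s | w = 1.2 | w = 1.5 |
|---|---|---|
| 0.50 | 1.000 | 1.000 |
| 0.52 | 0.993 | 0.984 |
| 0.55 | 0.982 | 0.961 |
| 0.60 | 0.964 | 0.923 |

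**4. How likely such splits are.** Under simple 1:1 randomisation with two waves of 522/2 = 261, the standard deviation of the difference in early share is √(2 × 0.25/261) = 0.044. The 10-point gap of the s = 0.55 case is then about 2.3 standard deviations (two-sided p about 0.02). A 4-point gap (s = 0.52) is about 0.9. Restricted allocation would make both rarer.

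**The case against.** The strongest objection is that this is a condensed article with a short analysis section. Its list is introduced as covariates that may potentially be used, which does not exclude wave, and an analysis plan that is not shown could add it. That stands in part: the list cannot be read as a final model. But the article does more than stay silent. It names specific factors, region among them, and leaves out the one factor it says the trial was randomised within. It also appeared in 2013, after the earthquakes it describes.

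The second objection is size. Each wave's first winter has concurrent early and late groups, so winter and earthquake are balanced between arms in expectation. The precision loss is small and the error is on the conservative side. This stands in full and limits the point to a modest improvement.

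Two stronger readings are tempting. A reader might infer that the earthquakes, or the difference between winters, bias the estimated subsidy effect. The documents do not support this, because allocation was randomised within wave. A reader might also infer that the earthquakes struck one region in one wave only. That is true only if each wave's first winter alone is analysed. Wave 1 was still in the study in 2011, so Christchurch participants of both waves were exposed. For the same reason a Christchurch-by-wave term does not substitute for a before-and-after term once second winters are included.

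**Conclusion.** The point holds in a limited form. The only stated randomisation stratum is absent from the named covariates, and including it always would be a real improvement at almost no cost.

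With 1:1 allocation within wave there is no built-in bias. The model standard error is larger by roughly 0 to 5%, at most about 4 points of power are lost under the largest effects assumed (counting the wave-by-region term), and inference is slightly conservative.

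A distortion of the estimate needs both a rate difference between waves and an uneven early share. The null ratio of about 0.96 rests on an assumed 1.5-fold wave difference and assumed splits of 55:45 and 45:55, which would be unusual by chance. With equal splits the distortion vanishes.

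The earthquake term belongs in a sensitivity analysis. It is not the correction of an error in the primary comparison.

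**What to change.** State under Data analysis that wave enters every early-versus-late comparison as a fixed covariate, not as one candidate among several. If second winters are analysed, add calendar winter as a separate factor.

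As a sensitivity analysis, add an indicator for Christchurch after September 2010 and report the subsidy effect with and without it. In a first-winter analysis this is the same as a Christchurch-by-wave term; otherwise the dated indicator is the one to use. Repeating the analysis without Christchurch in 2011 is an optional further check.

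The cost is one or two sentences and a few degrees of freedom: one for wave, two for three winters, one for the Christchurch indicator. The data are already held, and the simulation shows no loss when wave has no effect.

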**Figure 1 F1:**
[figure not shown]
Flow of participants through the study.

**Figure 2 F2:**
[figure not shown]
**Study timeline.** The wave design and randomisation meant that the interventions were spread over three years.

### Participants

The demographic characteristics of the 522 COPD participants enrolled are presented in Table 1; 20% were Māori, 77% New Zealand European or European and 2% Pacific peoples, and 3% reported belonging to other ethnic groupings, with only 3% of people reporting more than one ethnicity. We used the ethnicity classifications recommended by Statistics New Zealand. We succeeded in recruiting an older population (median age 71), with nearly a fifth (18%) of participants being over 80 at baseline.

**Table 1 T1:** Baseline characteristics of participants

**Characteristic**	**% (number)**
General health fair or poor	47% (216/460)
Phlegm most days a week	52% (239/458)
Shortness of breath most days a week	62% (288/461)
4 or more bouts of severe chest trouble over winter	22% (99/457)
Able to walk only 100m or less on the flat before stopping for breath	42% (192/457)
At least one cold/flu over winter	65% (294/453)
Ever told have heart disease	47% (210/446)
Ever told have at least 2 of heart disease, cancer, liver disease, renal disease, diabetes, arthritis	42% (179/430)
On home oxygen	8% (39/460)
Received flu vaccine	84% (387/458)
Received pneumonia (pneumococcal) vaccine	22% (96/420)
Lived in dwelling for more than 9 years	63% (290/463)
Dwelling built before 1977	72% (303/422)
Own the dwelling	76% (350/462)
Dwelling always cold	42% (196/462)
Cold at least partly to keep cost of heating down	48% (213/445)
Shivered inside at least once previous winter	56% (249/445)
‘Dragon breath’ inside at least once previous winter	39% (177/450)
Plug in medical equipment	21% (94/454)
Gave “no other choice” as a reason for main form of heating	43% (193/450)
Gave cheap or easy to budget with as reason for main form of heating	29% (129/450)
Eligible for a high use health card*	60% (251/416)
Eligible for community services card **	77% (337/438)
Receive a disability allowance	51% (220/435)
Currently smoke daily	17% (81/463)
European ethnicity	77% (349/452)
Māori ethnicity	20% (92/452)
Pacific ethnicity	2% (10/452)
Male	50% (228/456)
Aged under 65	27% (122/455)
Aged over 80	18% (81/455)
Median age	71 Years

*This card entitles some frequent users of health services to reduced health co-payments.

** This card entitles people on low income to reduced health (and some other) co-payments.

Initially the intention was to accept people into the study whose post-bronchodilator spirometry results demonstrated GOLD stage II (moderate) COPD or worse (GOLD, 2005). However, the logistics of conducting high quality spirometry in the homes of COPD patients created a recruitment bottleneck, stalling the study progress. Instead, two extra questions^a^ were added to the application form to identify people who had suffered a ‘moderate’ or ‘severe’ exacerbation of COPD as defined by the ATS/ERS Taskforce [63], and were therefore considered at risk of subsequent exacerbations. Thereafter, those who had been admitted to hospital for COPD and/or taken steroids or antibiotics for COPD within the last three years were considered eligible.

Other essential requirements were for applicants to be living in the community, in a household responsible for its own electricity bill, and with the intention of remaining in the same house for the duration of the study. In recognition of the earlier onset of COPD morbidity and mortality for Māori, study participants had to be 55 years of age or older, although applicants of 45 years or over were considered if referred on the specific recommendation of community health workers.

Co-morbidities were not exclusion criteria, unless the co-morbidities rendered the participant unable to communicate effectively. Co-morbidities are to be expected in this age group and, to be effective, an intervention must improve COPD in the presence of co-morbidities. We used a Charlson style index [64-66], modified to be based on self-report rather than ICD codes, to measure co-morbidities. Forty-two percent of baseline respondents reported having been told that they had two or more of: heart disease, cancer, liver disease, renal disease, diabetes and arthritis; 47% reported heart disease.

Using fuels other than electricity for heating was not an exclusion criterion, but participants were informed that only electricity bills would be credited. As we were attempting to model a possible population–level intervention, we wanted to have as broad inclusion criteria as feasible.

All participants were encouraged to be vaccinated annually against influenza, but this vaccination had to be obtained through their own GP or respiratory physician as part of the standard health-promotion campaigns. Eighty-four percent of baseline participants reported having had a flu injection for the most recent flu season and 22% reported a pneumococcal vaccination in the last five years.

In 171 households a support person also provided baseline information. These people completed a short questionnaire on the burden (if any) of providing care for the COPD participant, as well as the carer’s general health.

### Setting

The study was set up in three predominantly low-income urban areas. This study was carried out in partnership with local organisations with an interest in health and housing [44]. These organisations included a Māori health provider, a District Health Board, and Primary Health Organisations. Two communities were in the lower North Island (Whanganui and Wellington) and one in the South Island (Christchurch). Contracts were negotiated with these providers, who then worked closely with the research team, employing local field workers, nurses or community nurses, trained to conduct spirometry and administer the questionnaires.

One of the community organisations, Tu Kotahi, a Māori Asthma and Respiratory provider operating under the umbrella of Kokiri Marae, a large urban-based *marae* (communal meeting place), has participated in our two previous community housing trials. Our partnership is seen as resulting in many positive outcomes for both parties. For the Tu Kotahi Māori community it has brought insulated homes, improved heating, minimising the effects of allergens and increased information about healthy housing; for the University researchers it has provided access to the considerable knowledge of the community, as well as capacity building for both individual researchers and research groups.

Tu Kotahi’s involvement in housing research projects has highlighted the effects of poor housing on the health of their *whānau* (extended family community). In 2007, Tu Kotahi established a Māori COPD support programme and an important aspect has been the focus on healthy housing. Being research partners in this study has enabled Tu Kotahi to work more closely with *whānau* in their homes to assess their health status prior to, during and following the winter period, which has brought benefits beyond the study participation.

“The opportunity to follow up utilising our own community health worker has been crucial to maintaining the majority of *whānau* on the study. We have experienced a transient population during the study and this has often meant that we have only been able to locate *whānau* with information provided by the community health worker’s networks. Often, we discover that [members of the] *whānau* have been hospitalised or they have had to travel home for *tangihanga* (funerals). We also discovered how socially isolated a number of *whānau* are, this sometimes involved numerous visits before the door was opened for the community health worker to complete the study questionnaire and tests. We were also saddened at the number of *whānau* who passed away during the study; many of the *whānau* who participated experienced other co-morbidities that impacted on their respiratory conditions.”

The South Island provider, Community and Public Health, is the public health unit for the region of Canterbury. Staff also had a well-established working relationship with the researchers. Since 2001, these staff also carried out their own local health promotion strategies connected to housing improvement. Working with the researchers was therefore considered a mutually worthwhile undertaking in terms of developing opportunities for public health action.

In September 2010 the first of a continuing series of earthquakes and aftershocks occurred in Christchurch and the surrounding area [67]. With considerable fortitude the Christchurch team did not let the earthquake, aftershocks or widespread liquefaction disrupt the spring visits by the field workers. In February 2011 a major earthquake caused a massive collapse of buildings and 185 lives were lost [68].

Workplaces in the CBD were severely damaged and the area was closed to the public. The city’s infrastructure was in chaos as hundreds of organisations and businesses had no premises to work from, including the staff of Community and Public Health. This had an impact on the WHEZ study in a number of ways and the community researchers set about trying to overcome the subsequent problems.

Researchers agreed it was necessary to postpone interviewing for a three-week break to re-establish basic infrastructure and solve serious logistical problems. Laptops and other research equipment were initially out-of-bounds in the damaged office and only salvaged much later; however, the main computer system remained intact and data could be accessed remotely. The researcher’s home served as the research hub for the next year. There was only minimal disruption to the household visits when a further round of massive aftershocks and liquefaction occurred in June 2011. While the seismic activity has continued, it has diminished in intensity.

There was damage to the homes of the field workers and many participants, including chimney damage making fireplaces unusable, and structural damage affecting homes’ weather-tightness. There was also significant damage to infrastructure such as water, power lines and sewerage. For instance, because of damaged sewer lines in her neighbourhood, one field worker had to rely on a portable toilet on her street front for many months.

Some participants in the WHEZ study vacated their houses to a safer place for a period of time. Some moved to the less affected western suburbs or moved out of Christchurch for a number of weeks until they felt it was safe to return and this made it difficult for field workers to track participants down. Driving to the participants’ homes became laborious due to the extensive damage to roads. The study protocol stating that anyone who moved could not remain in the study was modified for the Christchurch participants; because so many other housing related variables had changed for many of the participants, there was little point in insisting on address stability. We also did not think it ethically appropriate to withdraw the fuel subsidy from participants who were forced to move because of the earthquake, but were otherwise keen to continue with the study.

The earthquake and continuous aftershocks were an emotionally traumatic experience for the participants, field workers and the co-ordinator. Financial worries about damaged housing, fear, and uncertainty about personal safety all contributed to this. The arrival of winter heightened people’s fears about the adequacy of the damaged electricity network to supply enough energy for households to be warm in winter. The field workers commented on the fears expressed to them during the research visits. The authorities were contacted for help in some desperate cases of damaged homes and heaters. Over the region, 9,000 new heaters were installed in the homes of people who had lost their primary heat source, and were paid for by the householder’s insurance company.

